#### Secondary objectives

2.2.2

Secondary objectives are to:– Measure changes in cognitive assessment scores by group between baseline and EOI assessments (standardised interval of 5 weeks apart), to allow comparison of effect sizes between groups.– Measure changes in cognitive assessment scores by group between EOI and 8-week follow-up assessments, to allow comparison of effect sizes between groups.– Measure changes in participant-reported effects on cognition by group between baseline, EOI, and 8-week follow-up assessments, to allow the comparison of effect sizes between groups.– Explore (at the follow-up interview) participant views on meaningful change in cognition in relation to the demands of trial participation.– Measure changes in scores for anxiety, depression, and fatigue before and after intervention, to allow comparison of effect sizes between groups.– Measure changes in the effective connectivity between left DLPFC and left caudate nucleus, to allow correlation with changes in cognition.

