**Figure 1 j_med-2023-0814_fig_001:**
[figure not shown]
Trial flowchart.

Consenting procedures will be conducted by the research psychologist. Participants will be randomised after completing the consent form, and the research psychologist will be blinded to group allocation. Participants will be randomised to one of four groups in equal proportions (1:1:1:1 ratio) automatically using blocked stratified randomisation, stratified on: age group (≤40), gender (man or woman), and MS type (relapsing-remitting MS or secondary progressive or primary progressive MS). The randomisation schema was created on 9th November 2021 10:51 using *ralloc.ado* version 3.5.2 [27] in Stata version 17. The neuromodulation research fellow is notified of the group allocation via an automatic email. The research psychologist and principal investigator will remain blinded to group allocation. The two TMS operators (including the neuromodulation research fellow) administering the iTBS will not be blind to group allocation.

Participants will be blinded as to whether their iTBS intervention is real (groups 1, 2, and 3) or sham (group 4) until the end of their study participation. Although only the 2-week intervention duration has a sham comparator (group 2 = real iTBS, group 4 = sham iTBS), participants will not be made aware that the 1- and 4-week intervention durations do not have a sham comparator. Participants will be instructed not to tell the research psychologist the duration of their intervention, as this would reveal to the research psychologist that the patient received the real iTBS intervention if in the 1- or 4-week intervention groups. To standardise the assessment interval and maintain the blinded status of the research psychologist, the interval between baseline and EOI assessments will be fixed at 5 weeks, requiring commencement of the iTBS intervention to be staggered per group as per Figure 2.

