#### 8-Week follow-up

2.6.6

At 8-week follow-up, participants will complete again the cognitive assessments and questionnaires (except for the EHI), followed by a semi-structured interview exploring the acceptability and tolerability of the intervention and any self-reported changes in cognitive ability experienced in daily life. The interview will also explore participants’ views on what a sufficiently meaningful and durable change in cognitive performance is to balance and justify the demands of the intervention (i.e., daily hospital visits, possible discomfort, etc.) Participants will be asked for suggestions for improving the trial experience.

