### Sample size

2.8

We aim to randomise up to 40 participants (up to 10 participants per group), which should provide sufficient information to inform our feasibility objectives and to inform the design of a potential phase III RCT. Whitehead et al. [45] recommend that pilot trial sample sizes should be between 10 and 20 participants per intervention group, to offer 80% power and two-tailed 5% significance level for standardised effect sizes of small (0.2) or medium (0.5). Therefore, with our acknowledgement that the study procedures may be taxing for people with MS, we have selected the smaller target of 10 participants per group to minimize inconveniences for a wider sample, with respect to our primary objective.

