### Data analysis plan

2.9

Data will be reported according to the CONSORT 2010 statement, extension for pilot and feasibility trials [46]. The research psychologist will perform the scoring cognitive tests and questionnaires scores and collation/tabulation of other endpoints prior to unblinded group analysis. Quantitative data will be analysed using SPSS version 24.0 [47]. We will provide descriptive statistics regarding the characteristics of the participants. Rates of consenting participants, recruitment, intervention completion, acceptability, tolerability, and adverse events will be reported by group on an intention-to-treat analysis (excluding participants who withdrew from the trial before the first iTBS administration).

Quantitative analysis will be used to evaluate the change in cognition, mood, and fatigue using the cognitive assessment and questionnaires. Where appropriate, parametric or non-parametric statistics will be used to estimate effect sizes and perform between-group comparisons to inform power and sample size calculations for a potential future phase III trial.

Qualitative data (post-intervention interviews) will be analysed using framework analysis [48–51]. These will be audio-recorded and transcribed verbatim by the research psychologist. The interview transcripts will be mapped onto a predefined framework. An analytical framework will be developed according to the interview schedule which will map onto the aims of the qualitative study. The researcher will read the transcripts to get familiar with the content of the interview. Subsequent analysis will be conducted on NVivo software [52]. This process will follow Gale et al.’s guide to framework analysis [48]. Following the initial coding of the first transcript, two researchers will meet to discuss the codes and to check whether the coding is consistent and comprehensive. Disagreements will be resolved through discussion together or with a third member of the study team to prevent bias. Once all the coding is completed, the researcher will enter these data onto the framework matrix and determine the fit of the data to this matrix. Any new data that does not fit the matrix will be considered again to see whether a new thematic structure is needed to include such data.

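### Observed effect sizes from arms of up to 10 are named as inputs to the phase III sample size, but are too imprecise for that use and could badly mis-size the next trial

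*Protocol article*

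**What the plan says.** Section 2.9 (Data analysis plan) gives the purpose of the quantitative analysis, by whichever type of test suits the data, as follows: "estimate effect sizes and perform between-group comparisons to inform power and sample size calculations for a potential future phase III trial". Section 2.2.2 (Secondary objectives) repeatedly gives the comparison of effect sizes between groups as the reason for measuring change in cognition, self-reported cognition, mood and fatigue.

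Section 2.8 (Sample size) sets the size: "We aim to randomise up to 40 participants (up to 10 participants per group", in four equally allocated arms. Three arms receive iTBS for 1, 2 or 4 weeks. One receives sham for 2 weeks.

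Two other places bear on the phase III target. Section 2.2.2 plans to explore "participant views on meaningful change in cognition in relation to the demands of trial participation". The interview in section 2.6.6 asks "what a sufficiently meaningful and durable change in cognitive performance is to balance and justify the demands of the intervention". Neither is linked to the phase III sample size. The only quantitative inputs that section 2.9 names for that calculation are effect sizes and between-group comparisons.

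**The concern.** A sample size varies with the inverse square of the assumed effect, so an error in the effect becomes a larger error in the sample size. With up to 10 per arm the observed effect may be far from the true one in either direction. An overestimate leads to an underpowered phase III trial. An underestimate leads to one that is needlessly large, and a zero or negative estimate gives no sample size at all. Informing the phase III design is a stated purpose of this trial (sections 2.1 and 2.8), so the weakness lies on the path to one of its main products.

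**Working it through.** **Inputs.** n = 10 per arm and four equal arms (sections 2.4 and 2.8). Two-sided 5%, 80% power and standardised effects of 0.2 and 0.5 (section 2.8). No SD is given, so effects are in SD units. Assumed: normal outcomes, common variance, no dropout unless stated.

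**1. The plan's own figure.** Section 2.8 cites a recommendation that "pilot trial sample sizes should be between 10 and 20 participants per intervention group", said "to offer 80% power and two-tailed 5% significance level for standardised effect sizes of small (0.2) or medium (0.5"). Taken literally, as the power of the pilot, this does not reproduce. The noncentral t gives:

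| n per arm | d = 0.2 | d = 0.5 |
|---|---|---|
| 10 | 7% | 19% |
| 20 | 9% | 34% |

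At 10 per arm, 80% power needs d = 1.32. If the 80% is meant for the later main trial, it rests on a source not at hand and cannot be checked here. Under either reading, between-group tests in this trial have about 19% power at d = 0.5.

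**2. Precision of the estimate.** SE(d) ≈ √(2/n + d²/(4n)). For n = 10 and d = 0.5 this is √(0.2 + 0.00625) = 0.454, and 1.96 × 0.454 = 0.89. The exact 95% interval for an observed d of 0.5 is −0.40 to 1.38.

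**3. Needed size of the next trial.** n per arm = 2(1.96 + 0.842)²/d² = 15.70/d². At d = 0.5 this is 62.8, so 63. At d = 0.2 it is 392.4, so 393.

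**4. What the pilot would imply at a true d of 0.5, for one contrast.** The approximate SE is √(2/10) = 0.447.

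- Less than half the needed n requires an observed d above 0.5 × √2 = 0.707. z = (0.707 − 0.5)/0.447 = 0.463, probability 32%.
- More than twice the needed n, or no usable n, requires d below 0.5/√2 = 0.354. z = (0.354 − 0.5)/0.447 = −0.327, probability 37%.
- An estimate at or below zero: z = −0.5/0.447 = −1.118, probability 13%. These cases are part of the 37%.
- Together, 32% + 37% = 69% of pilots miss by more than a factor of two; about 31% do not.

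Simulation with 400,000 pilots, the SD estimated from all four arms, gives the same 32%, 37% and 13%. The quartiles of the observed d are about 0.20 and 0.82. They imply 15.70/0.20² = 393 and 15.70/0.82² = 24 per arm, against 63. The mean estimate is 0.51, so a single contrast is imprecise but almost unbiased. Among positive estimates, the median actual power of the resulting trial is 69%. With 8 per arm analysed, the 32% and 37% become 34% and 38%.

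**5. If, in addition, the largest of three contrasts were used.** With three equally effective arms sharing one sham group, the expected excess is about 0.85 × √(1/10) = 0.27 SD. The simulation gives a mean of 0.78 at a true 0.5 (bias 0.28), a median n of 26 per arm against 63, and a median actual power of 44%.

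**6. What the pilot can supply.** The SD pooled over four arms has 4 × 9 = 36 degrees of freedom. Its 95% limits are √(36/χ²), that is 0.81 to 1.30 times the estimate, and the one-sided 80% upper limit is 1.12 times. Using that limit raises the phase III sample size by 1.12² = 1.25, or about 25%. With 8 per arm (28 degrees of freedom) the limit is 1.14 times.

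**The case against.** The text says that the estimates will inform the calculation, not determine it, and it does not rule out using confidence intervals or SDs. The effect estimates are secondary; the primary objective is feasibility, acceptability and tolerability. Exploratory comparisons are not wrong in themselves. This limits the wording: phase III could be mis-sized, not that it will be. It does not remove the point, because section 2.9 names no other quantitative input.

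A reader might infer three stronger things that the document does not support.

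- **That the best-looking schedule will be picked.** No section says so. Section 2.1 compares the schedules on feasibility and acceptability, and section 2.4 makes clear that only the 2-week schedule has a sham arm of matching duration. The upward bias in step 5 arises only if the schedule or contrast is chosen on its effect.
- **That a poor estimate would stop the programme.** The protocol has no efficacy-based go/no-go rule, so the 13% of pilots at or below zero trigger no stated decision.
- **That the resulting sample size would be close to random.** About 31% of pilots fall within a factor of two of the needed size.

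The interviews are also not a ready substitute. They are semi-structured and analysed by framework analysis, and the protocol gives no way of turning them into a numerical difference on a cognitive test.

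**Conclusion.** The point holds in limited form. An observed effect from arms of up to 10 should not set the phase III target difference. At a true effect of 0.5, about one third of pilots would imply less than half the needed sample size, and a little over one third would imply more than twice it or none. Imprecision alone produces this; the finding does not depend on selection among arms. The figures assume normal outcomes with common variance, and 10 analysed per arm; dropout makes them somewhat worse. At a smaller true effect the miss is also larger: at 0.2, 43% of pilots imply less than half the needed 393 per arm, and 45% imply more than twice it or no usable number. This is an inexpensive improvement to a stated method and does not affect the primary feasibility objective.

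**What to change.** In section 2.9, replace the sentence linking effect sizes and between-group comparisons to the phase III calculation with the following commitments:

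1. The phase III target difference will not be set from the effects observed in this trial.
2. Between-group differences will be reported with 95% confidence intervals as descriptive or exploratory results, without reliance on significance tests.
3. This trial will supply the pooled within-group SD of each candidate outcome with an upper confidence limit (one-sided 80%: 1.12 × SD at 36 degrees of freedom, somewhat wider with dropout), the baseline–follow-up correlation, and retention.
4. The target difference will rest on a pre-specified meaningful change, with the interview views from sections 2.2.2 and 2.6.6 as supporting input and not the sole source.

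Choosing the schedule on feasibility and acceptability is consistent with section 2.1 and needs no change. A sentence saying that it will not be chosen on observed effect would close off the conditional bias.

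The cost is wording only: no new data and no extra visits. It can be done before the unblinded group analysis. The downside is that no pilot-based effect size or p-value is carried into the phase III calculation, and that a meaningful difference has to be justified separately.

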#### Data synthesis

2.9.1

Quantitative and qualitative data will be synthesised following the convergence coding matrix strategy [53,54]. The research team will complete the quantitative and qualitative analysis separately, and then use a convergence coding matrix to synthesise the findings.

The research team will identify the key factors that provide insight regarding the impact and acceptability of the intervention. The research team will then look for agreement or disagreement between the findings from the different research methods.

The convergence coding matrix follows four possible codes [53,54]:Convergence: Agreement between the data from both methodologies.Complementary: The findings from one methodology complement the rest of findings.Disagreement: The findings from each methodology contradict each other.Silence: Only one methodology offers information of a key finding.

### Patient and public involvement

2.10

Patient and Public Involvement (PPI) representatives have been involved from the inception of the project. This project was presented and discussed at the Nottingham MS PPI group meeting in March 2019. Attendees were asked to rate the relevance of the study and methods used; the attendees believed that the study was highly relevant, and the planning was excellent.

The research team also includes two PPI representatives who contributed to the development of the grant proposal and are involved in the review of participant-facing material, research team meetings to discuss progress, and commented on manuscripts for appropriateness of language.

### Dissemination

2.11

The findings from this study will be disseminated to relevant stakeholders (e.g., people with MS and their families, healthcare professionals). A main manuscript reporting the feasibility of delivering the proposed intervention and outcomes will be submitted for publication. The findings will also be disseminated at national and international conferences to reach a wider academic audience. Finally, we will share the findings with organisations that work with people living with MS (e.g., MS Society) by writing a lay summary report or presenting at conferences organised by and for people living with MS (e.g., MS Life conference)

### Trial status

2.12

Recruitment commenced on 22 June 2022. At present, 32 potential participants have been screened, 24 have been recruited, 14 have completed the intervention (or sham), and 13 have completed the 8-week follow-up assessment.

**Ethical approval:** The study received a favourable ethical opinion from the Health Research Authority (ref: 21/LO/0506) on 20 August 2021. The study is registered with ClinicalTrials.gov (NCT04931953).

## Conclusion

3

This manuscript reports the study protocol for mixed-methods feasibility randomised controlled trial exploring the feasibility and acceptability of iTBS improving for cognitive performance in people with MS. Data regarding the feasibility and acceptability of the intervention will be collected using mixed methods research to allow for an in-depth understanding of the impact of the intervention and identify barriers for future implementation in a larger phase III RCT.
